### 2.11. Data Management Plan

The data management plan is provided in Supplementary Material 1. The type and format of data that will be collected and generated within the scope of this project is described in this plan, together with the procedure provided to access data (by whom, how, and when it can be accessed), data ownership, repository to deposit data, and procedure planned to guarantee the specific ethical and legal requirements.

Details of the Data Protection Impact Assessment (DPIA) will also be presented here in accordance with the specific adaptation of this methodology to research projects in the health care sector [87,88,89]. Thus, the need for a DPIA was confirmed from the outset (Table S1). Subsequently, the data lifecycle was defined (Table S2), and the need and proportionality of the processing were analysed (Table S3) and, finally, a risk assessment and action plan developed (Table S4).

## 3. Discussion

Given the characteristics, current and future repercussions of the current pandemic, developing this research project will make it possible to periodically obtain relevant information for decision-making processes in social and health matters and, therefore, promote a more efficient, reliable, and responsible science for social change (such as the one that we are currently experiencing as a result of the pandemic). In addition, it will encourage:institutional alliances of great social value between the public administration, health care services, and the scientific and academic community;powerful and novel methodologies in the fields of public health, epidemiology, and sampling to reduce potential biases caused by a lack of coverage, response, or non-randomised selection [1,50];large, integrated, quality, and open databases containing information extracted from clinical and non-clinical population registries; data concerning social, economic, and environmental contexts and the perception of the population, along with foreseeing the future incorporation of genomic information [90];the systematic review throughout the entire project of the scientific evidence obtained through this type of study;training with a view to transmitting the available knowledge and increasing capacities and skills in designs, sources, and methodologies;measuring the short- and mid-term impact of COVID-19 at different times and on different populations since the beginning of the official State of Alarm.

The limitations of the study include those derived from the coverage and quality of the sampling frames, which may cause selection biases. In the case of the BDLPA, its telephone coverage is over 90% and it tends to have low percentages of non-existent telephone numbers (7–8%) or non-contactable telephone numbers due to the frame’s outdatedness (9–10%). That said, any potential biases due to such defects will be corrected through the estimator calibration techniques described above. Another limitation is that caused by the longitudinal design of the ESSOC surveys in terms of panel attrition, which could lead to potential biases due to an absence of response. We estimate the response rate for the full longitudinal sample to be 25–35% (the effective sample in M5 of the effective sample in M1 is divided by the effective sample in M1). To reduce the effect of potential non-response biases, we decided, on the one hand, to use an overlapping panel design as this type of design allows for completing each measurement with new cross-sectional samples that become longitudinal in subsequent measurements and, on the other hand, to make adjustments in each measurement according to the weights of the longitudinal samples.

This study was initially designed to also include population from nursing homes, but ultimately this was not possible. This is an unfortunate limitation of the study considering the enormous impact that COVID-19 has had on this population. In addition, this project may have information biases intrinsic to sampling research. Consequently, we have chosen to employ scales and variables widely used in population-based health surveys and that also allow comparisons to be made for most of the key indicators. Finally, as in most of these types of studies, its feasibility and limitations will, to a large extent, depend on the quality and availability of the data from different data holders. Data availability for this project would appear not to be a limitation, given that the request for the processing of these data is in accordance with the policies on data disclosure for processing data in research projects in the public sector. Additionally, the EIPD performed resulted in an acceptable residual risk level (see Supplementary Material 1). This evaluation highlights, among other elements, that the data provided is protected by statistical confidentiality, that it is not misused, that its treatment is anonymous and global at all times, and that indirect identification is impossible. Furthermore, the project’s results will be beneficial to the general population in a holistic way, thanks to its socioeconomic and environmental context, and its evolution over several years from the onset of the pandemic. Therefore, the risk to the privacy of the study population is minimal compared to the potential benefits the results will bring. The transfer of data will be carried out between organisations within the Junta de Andalucía, as this will be within the context of a research project exclusively in the public sphere and under the legitimate use of records as research infrastructures in accordance with the Spanish health legislation (see Supplementary Material 1). With respect to data quality, the reproducibility of this research will be conditioned by the way in which the data have been obtained, a phenomenon common to all RWD studies. Even when these are the best possible, the fact that the data are extracted from official sources does not guarantee their quality. Due to this, the owners of the information will be asked to describe the detailed procedure used to extract the data, as well as any previous processing it may have undergone. It should be noted that individuals collaborating on this project also belong to the work teams of the main sources of information to be used which, therefore, should guarantee success in the interpretation of the original data and the optimisation of the extraction strategies.

## 4. Conclusions

The ESSOC will enable precise and valid analysis of the short- and mid-term impact of the policies applied, and interventions made to, not only of the health of the general population, but also the most vulnerable population, during the pandemic. The study will also determine the evolution of the socioeconomic, psychosocial, behavioural, occupational, environmental, and clinical determinants of health, and identify the inequalities in health in all its axes (i.e., social class, gender, age, ethnicity, and territory).

The conceptual approach of this study will encompass all aspects affecting health and so will contribute to an extraordinary increase in the current knowledge concerning the impact the COVID-19 pandemic is having. This knowledge will, in turn, be crucial for health systems to be able to design quick and effective interventions aimed at improving the health care, health, and quality of life of the populations most affected by the COVID-19 pandemic. Moreover, the project management model based on collaborative, multidisciplinary, and open research will allow the critical mass needed to be generated to thus achieve the objectives that have been set (i.e., at the populational level, as well as at an individual and disease level, in our case, COVID-19).

## Figures and Tables

**Figure 1 ijerph-18-08120-f001:**
[figure not shown]
Health Care and Social Survey (ESSOC): Population and Temporal Scope, and Samples based on an overlapping panel design (Response Rates of the measurements already taken are calculated only with the negatives, the rest of them are calculated with all kinds of fieldwork incidences).

**Table 1 ijerph-18-08120-t001:** Health Care and Social Survey (ESSOC): Study Framework.

Focus	Design	Dissemination	Management
Public Health	Real-World Data	Open Science	Collaborative and Multidisciplinary Research
Community participation to obtain information on people’s health and quality of life to be able to intervene both individually and collectively in the face of the pandemic	Integration of observational data extracted from multiple sources from different perspectives based on probabilistic samples and administrative registries	Results, methodologies, processes, and collected data distributed, reused, and freely and openly accessible	Andalusian School of Public Health, Andalusian Health Service, Department of Health and Families (Andalusian Regional Government), Universities of Granada and Girona, Andalusian Institute of Statistics and Cartography and Guadalinfo Network

**Table 2 ijerph-18-08120-t002:** Health Care and Social Survey (ESSOC): Interview incidences and protocol to be followed:

Incidence	Incidence	Description	Protocol
Frame incidence (reasons that make it impossible to complete the survey due to problems related to the sampling frame; for example, a telephone number with which to contact the sample person could not be obtained or the housing frame was not sufficiently up to date).	The telephone number does not exist.	Wrong number: the telephone number dialled does not exist, corresponds to a fax, or has restricted calls.	Direct removal.
	Not contactable.	Out-of-date frame: the selected person is living in a different municipality, a telephone frame without a telephone number, a person unreachable through the telephone number/home address provided due to circumstances such as death, divorce/separation, etc.	Direct removal.
Relationship-situation incidences (reasons that make it impossible to complete the survey due to several types of situations affecting the surveyed people, for instance, they cannot be located, they refuse to participate in the survey, or any other aspect that prevents the survey being conducted).	No contact.	The household cannot be contacted (e.g., nobody answers the telephone, or the answering machine goes off).	Removal after four attempts performed on two different days, at two different times.
	Absent.	The selected person cannot be contacted.	Removal after four attempts performed on two different days and at two different times.
	Inability to answer.	The selected person cannot complete the survey due to an inability to respond to it because of disability, age, illness, lack of knowledge of the language, or any other circumstance. If possible, the survey should be completed by a close relative.	Direct removal.
	Refusal.	The selected person refuses to complete the survey or refuses to continue it after it has begun.	Direct removal.

**Table 3 ijerph-18-08120-t003:** Health Care and Social Survey (ESSOC): Adjustment of the design sampling weight in each measurement.

	Type of Adjustment	
Sample Type (Effective)	1st Phase	2nd Phase
New	Non-response adjusted by proxy based on the effective sample size in each stratum.	Representativeness by truncated linear calibration with 0.1 and 10 limits based on the auxiliary variables
Longitudinal	Non-response adjusted using an XGBoost model based on variables from the previous measurement.	

**Table 4 ijerph-18-08120-t004:** Health Care and Social Survey (ESSOC): Auxiliary sources and variables.

Registry	Description	Information	Variables Extracted
BDLPA–Longitudinal Andalusian Population Database [71]	Information from the census coordination system and civil registries that give rise to a consolidated framework of the Andalusian population	Personal data	Name, surname, identification health number (NUHSA), geographical coordinates
BDU–User Database of the Andalusian Public Health Care System [58]	Contact Information of the Andalusian Public Health Care System	Personal contact information	Telephone numbers
BPS–Andalusian Population Health Database [71]	Personal health information from the Andalusian Population Health Database and Health care information	Health and health care information	Chronic diseases, functional and cognitive assessments, health resources (volume and cost), population stratification, drugs consumed
REDIAM–Andalusian Environmental Information Network [72]	Daily averages by collecting/meteorological station and at the census section level	Pollution, temperature	Mean daily values from pollution, air quality and temperature
SVEA–Andalusian Epidemiological Surveillance System [73]	Functional organisation for health surveillance that collects, among other things, epidemiological information related to SARS-COV-2 infection	Epidemiological information of COVID-19	PCR results, symptoms’ date, close contact, health care professional, hospitalisation unit (specifying ICU), date of admission and discharge, need of mechanical ventilation and clinical data

For further details, see Supplementary Material 3.

**Table 5 ijerph-18-08120-t005:** Health Care and Social Survey (ESSOC): Information blocks and variables entered in each measurement.

Subject Area	1st Measurement (M1)	2nd Measurement (M2)	3rd Measurement (M3)	4th and 5th Measurements (M4 and M5)
Household and housing characteristics	Municipality, usual household, type of household, surface area, facilities, household changes, number of cohabitants (<6/<16/>60), type of household, and equipment.	Municipality, usual household, type of household, surface area, facilities, household changes ^b^, number of cohabitants (<6/<16/>60), equipment, number of rooms, and number of inhabitants with disabilities or requiring care.	Municipality, usual household, type of household, surface area, household changes, number of cohabitants (<6/<16/>60), number of rooms, and number of inhabitants with disabilities or requiring care.	Municipality, usual household, type of household, surface area, household changes, number of cohabitants (<6/<16/>60), number of rooms, and number of inhabitants with disabilities or requiring care.
Time use and cohabitation	Household chores, care tasks, daily activities during the confinement period (at home and outside), cohabitation and relationships, and causes for optimism.			Household chores, care tasks, daily activities ^b^ during the confinement period (at home and outside), cohabitation and relationships, and causes for optimism.
Health and emotional well-being	COVID-19 diagnosis, severity, diagnosis within the person’s settings, self-perception of general and mental health (current and last year), emotional well-being ^c^, difficulty to withstand the confinement, malaise, chronic illness, and change of medication.	COVID-19 diagnosis, severity, diagnostic tests, diagnosis within the person’s settings, self-perception of general and mental health, emotional well-being ^b^, cohabitation, difficulty to withstand the confinement, happiness, social and emotional support ^c^, malaise ^b^, chronic diseases (suffering and limitations), and medication (use and change of use ^b^).	COVID-19 diagnosis ^b^, severity, diagnostic tests, diagnosis within the person’s settings, self-perception of general and mental health, emotional well-being ^b,c^, happiness, social and emotional support ^b,c^, malaise ^b^, chronic diseases (suffering and limitations), and medication (use and change of use ^b^).	COVID-19 diagnosis ^b^, severity, diagnostic tests, diagnosis within the person’s settings, self-perception of general and mental health, emotional well-being ^b,c^, happiness, social and emotional support ^b,c^, malaise ^b^, chronic diseases (suffering and limitations), and medication (use and change of use ^b^).
Habits and lifestyle	Habit modification (exercising, smoking, alcohol consumption, sleep, and diet).	Habit modification ^b^: exercising, drinking, smoking, sleep, food, daily intake of vegetables and fruit, exercising, weight and height ^c^, smoking, alcohol consumption, sleep, and flu vaccination.	Habit modification ^b^: exercising, drinking, smoking, sleep, food, daily intake of vegetables and fruit, exercising, weight and height ^c^, smoking, alcohol consumption, sleep, and flu vaccination ^b^.	Habit modification ^b^: exercising, drinking, smoking, sleep, food, daily intake of vegetables and fruit, exercising, weight and height ^c^, smoking, alcohol consumption, sleep, and flu and COVID-19 vaccination ^b^.
Economic situation and socio-demographic characteristics	Educational level, employment situation, working from home, type of contract, occupation ^c^, cohabitation with a partner, identification of the cohabitant with the greater income (educational level, employment situation, type of contract, occupation), difficulty in making ends meet, late payments, income, future worries, and degree of confidence in public institutions.	Employment situation, educational level, occupation ^c^, development ^b^, ability to work, identification of the cohabitant with the greater income (educational level, employment situation, occupation), difficulty in making ends meet, late payments, change in economic situation, parents’ educational level, and future worries.	Employment situation, educational level, occupation ^c^, development, ability to work, identification of the cohabitant with the greater income (educational level, employment situation, occupation), difficulty in making ends meet, late payments ^b^, change in economic situation, parents’ educational level, and future worries.	Employment situation, educational level, occupation ^c^, development, ability to work, identification of the cohabitant with the greater income (educational level, employment situation, occupation), difficulty in making ends meet, late payments ^b^, change in economic situation, parents’ educational level, and future worries.

^a^ Questionnaires are provided in Supplementary Material 2. ^b^ Variables that present modifications in their temporal scope in relation to the previous measurement. ^c^ Composite variables: emotional well-being [75], social and emotional support [76,77], body mass index [78], social class [79,80].

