### 1.3. Hypotheses

Perceptions of general health, mental health, and emotional well-being could have deteriorated in the short- (one year) and mid-term (three years) since the beginning of the pandemic, with a greater impact perhaps being observed in women, young people, and those diagnosed with COVID-19.The socioeconomic, psychosocial, behavioural, occupational, environmental, and clinical determinants of health could have deteriorated since the onset of the pandemic.Health inequalities may have increased along the axes of social class, gender, age, ethnicity, and territory as a result of COVID-19, and may be even greater in the mid-term compared with the short-term.Chronicity and resulting disability may have increased significantly since the beginning of the pandemic.Since the beginning of the pandemic, the care burden has increased significantly for women in the short-term and this might have had a highly negative impact on their health and well-being.Social and emotional support in the population aged over 55 years might have decreased significantly since the beginning of the pandemic, with the greatest differences perhaps being observed in single-person households in urban areas.

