Sample size for the first measurement of the ESSOCgeneral was estimated according to a non-response rate of 40% (Figure 1). This response rate was considered as the percentage of surveys carried out or effective sample with respect to the total of the theoretical sample. Thus, this calculation includes in the denominator all types of incidents, that is, not only those directly related to the refusal of the selected person to be interviewed, but also to the following incidents:from the sampling frame (e.g., incorrect or unreachable telephone number, or person residing in a place other than the one selected);when conducting the interview (e.g., person who cannot be reached, appointment outside the fieldwork time, or insufficient number of attempts to finish the fieldwork, that is, most would be cases that would have answered the interview if it had been extended to the end of the fieldwork);leaving the cohort (e.g., deceased, long-term hospital admissions, change of residence etc.).

The reason for including all types of incidents in the response rate is to obtain a sufficient theoretical sample size to reach the effective sample size of 3000 interviews. This means that, once almost all the fieldwork of the longitudinal sample had been completed, a new sample was added until the total effective size of 3000 interviews was reached. When that sample size was achieved, the field work was completed at each measurement.

In short, if we take into account only the refusals of the selected person, our total response rates are above 70%. Moreover, the field work carried out has introduced elements of improvement that have allowed for an increase in the response rates from one measurement to the next, both for the longitudinal samples and for the new ones that were incorporated in each measurement.

Thus, for measure 1 of the general ESSOC, the response rate was 88.5%. For measure 2, it was for the longitudinal sample 78.3% and for the new one 58.2% (total 73.0%). For measure 3, it was 88.8% and 75.3%, respectively (total 83.1%), and for measurement 4 it was 91% and 78.2% (total 87.8%, Figure 1). 

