### 2.8. Sampling Weights

The original sampling weight for the new samples is obtained from the inverse values of the effective sampling fractions in each stratum and used to calculate the Hajek estimator [62]. This is subsequently calibrated to obtain more reliable estimates based on the demographic characteristics of Andalusia. To this end, we use a truncated linear calibration method [63] and, as auxiliary information, the marginals of the Andalusian population per sex and age (16–19, 20–24, 25–29,..., 75–79, and ≥80 years old), sex and province, sex and nationality (Spanish or dual nationality and foreign), and sex and degree of urbanisation. These data are obtained from the Continuous Municipal Register (Padrón Continuo de Municipios) [64]. Regarding the non-response bias in longitudinal samples, we can predict non-contact and non-cooperation based on auxiliary information and information already known about the sample subjects. Thus, the original weights used in the estimates of longitudinal sample M_t are corrected during a first phase by modelling the non-response with respect to the longitudinal effective sample obtained in M_t-1 using machine learning techniques [65]. Said non-response is estimated using a XGBoost model [66], which represents the state-of-the-art in machine learning. Every piece of data and variable from the M_t-1 sample is used for training; thus, the algorithm has all the information available to learn. Likewise, the hyperparameters of the model are optimized using cross-validation to ensure reliable estimations. Then, during a second phase, they are calibrated following the method described for the new samples. As auxiliary variables, we use those extracted from the Continuous Municipal Register (e.g., nationality, sex, age, province, degree of urbanisation, etc.) and the registers from the ESSOC itself in M_t-1 (Table 3).

In addition to these adjustments, other methodological alternatives, not yet explored in this type of sample design, for instance, double calibration, will also be investigated by considering different variables in order to model non-responses and, on the other hand, correction of the representativeness bias [67,68] and machine learning techniques, and adjusting non-responses with the aid of the Propensity Score Adjustment (PSA) [69,70].

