### 2.9. Variables

The study variables will mainly be extracted from the following sources: BDLPA; the Andalusian Population Health Database (BPS, Base Poblacional de Salud) [71]; the Andalusian Environmental Information Network (REDIAM) [72]; the Andalusian Epidemiological Surveillance System (SVEA) [73] and the ESSOCgeneral, ESSOCzones, and ESSOC + 55 surveys.

The personal data of the participants selected for the interview (name, surname, and telephone number) are extracted from the BDLPA. In addition, the BDLPA is linked annually with a repository of georeferenced buildings so that the postal address and coordinates (250 m × 250 m grid) in the territory can be extracted. This will allow us to extract geographical factors (urbanisation degree and population density, among others) via other IECA registries, and environmental factors (pollution and temperature, among others) via the REDIAM registry from the Andalusian Regional Government’s Department of Agriculture, Livestock, Fisheries, and Sustainable Development (Consejería de Agricultura, Ganadería, Pesca y Desarrollo Sostenible de la Junta de Andalucía).

From the SVEA registry, epidemiological information related to COVID-19, such as the date and result of the diagnostic test for active infection (PDIA), will be extracted to detect the presence of an active SARSCoV-2 infection, which includes both reverse transcription–polymerase chain reaction (real time RT–PCR) as the antigen (Ag) rapid test; date of the onset of symptoms; close contact of confirmed case with PDIA; local or imported case; occupation as a health or social health professional; need for hospitalisation or admission to an intensive care unit; date of admission, and discharge.

In addition, the clinical information related to chronic diseases [74], functional and cognitive assessments, health resources (volume and cost), population stratification, and drugs consumed, which is obtained from the BPS, will also be added to the valid samples (Table 4). Further information about the variables and the main features of the abovementioned registers can be found in Supplementary Material 3.

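### The panel non-response weights use only data from the previous measurement, so they cannot correct for COVID-19 infection or hospital admission between measurements, although registry data on both are to be linked

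*Protocol article*

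**What the plan says.** **Weights.** Table 3 describes the first-phase adjustment of the longitudinal sample as "Non-response adjusted using an XGBoost model based on variables from the previous measurement". Section 2.8 adds "Every piece of data and variable from the M_t-1 sample is used for training". The second phase calibrates to demographic margins from the Municipal Register "and the registers from the ESSOC itself in M_t-1 (Table 3").

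**Reasons for loss.** Section 2.4 counts among the incidents "leaving the cohort (e.g., deceased, long-term hospital admissions, change of residence etc". Table 2 includes inability to answer because of illness.

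**Outcome.** Hypothesis 1 (section 1.3) expects deterioration of health and well-being, "with a greater impact perhaps being observed in women, young people, and those diagnosed with COVID-19".

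**Registry data.** Section 2.9 plans to extract from SVEA the date and result of the infection test and "need for hospitalisation or admission to an intensive care unit; date of admission, and discharge". Clinical data from BPS are to be added to the valid samples. No section brings any of these into the weighting.

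**Room left open.** Section 2.8 also states that "we can predict non-contact and non-cooperation based on auxiliary information and information already known about the sample subjects", and that alternatives "will also be investigated by considering different variables in order to model non-responses". It names no registry variable in either place.

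**The concern.** A non-response weight removes bias only to the extent that its predictors capture what drives both dropout and outcome. Here the predictors stop at M_t-1, while the events of most interest in a pandemic panel happen afterwards. More M_t-1 variables or better tuning cannot recover an event that had not yet happened.

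The weights carry real load. The Discussion expects only 25–35% of the M1 respondents to be in the effective sample at M5, and it relies on weighting, together with refreshment samples, to limit attrition bias. The gaps are long: 18 months before M5 of ESSOCgeneral (month 12 to month 30), 12 months for ESSOCzones and 24 months for ESSOC+55 (section 2.2). Weighted panel estimates of change would be affected first.

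**Working it through.** **1. Can the event be known for people who drop out?** Section 2.5 makes the theoretical longitudinal sample at M_t equal to the effective sample at M_t-1. Every longitudinal dropout was therefore a respondent, and so in a valid sample, at the previous measurement. An event taken from a registry can be observed for respondents and dropouts alike, provided the linkage is run on the M_t-1 sample and not only on those who answer at M_t.

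**2. The design figure, as a yardstick.** Inputs from section 2.4: p = q = 0.5, precision 2.4 points, 95% confidence, design effect 1.8, non-response 40%.

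- Effective n = 1.96² × 0.25 × 1.8 / 0.024² = 3001.
- Theoretical n = 3001 / 0.60 = 5002.

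The stated 3000 and 5000 are reproduced. The point attacks neither figure.

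**3. Bias in a panel prevalence from an omitted event.** Let π be the share with the event, rr the response of people with the event relative to the rest, and D the outcome difference.

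Bias = [π·rr / (π·rr + 1 − π) − π] × D

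- π: section 1.2 gives almost 600,000 cases in one year and 8.5 million residents, so π = 7.1% if each case is a different person. Scaling by 1.5 to the 18 months before M5 gives 10.6%; this scaling is an assumption.
- rr from 0.5 to 0.9 and D from 10 to 30 points are assumptions. The article gives neither.

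| π | rr = 0.9, D = 10 | rr = 0.75, D = 20 | rr = 0.5, D = 30 |
|---|---|---|---|
| 7.1% | −0.07 | −0.33 | −1.02 |
| 10.6% | −0.10 | −0.49 | −1.50 |

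Entries are percentage points. The bias is zero if rr = 1, or if the event is in the model and response is random given it. Within these inputs the entries are upper values, because M_t-1 variables and calibration may already absorb part.

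**4. Illustration for a diagnosed/undiagnosed contrast.** All inputs are assumed: a share h = 5–15% of the newly diagnosed is admitted; response is r = 30% or 50% in the admitted and 75% in others; deterioration is 70% in the admitted, 35% in other diagnosed people and 30% in the undiagnosed.

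- True rate in the diagnosed = 0.70h + 0.35(1 − h)
- Observed rate = [0.70hr + 0.35 × 0.75(1 − h)] / [hr + 0.75(1 − h)]

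| h | True excess over 30% | Observed, r = 30% (loss) | Observed, r = 50% (loss) |
|---|---|---|---|
| 5% | 6.75 | 5.72 (15%) | 6.19 (8%) |
| 10% | 8.50 | 6.49 (24%) | 7.41 (13%) |
| 15% | 10.25 | 7.31 (29%) | 8.68 (15%) |

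The loss is 8–29% of the contrast. This calculation gives the undiagnosed group no illness-related loss, so the pull towards no difference is built in. In general the bias of the contrast is the bias in the diagnosed minus the bias in the undiagnosed, each from the formula in step 3. If event share, relative response and D were equal in both groups, the two would cancel; if illness loss weighed more in the undiagnosed, the sign would reverse.

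**The case against.** Several objections stand and limit the point.

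- **Death.** A reader might infer that death is another missing predictor, or that survivors are being weighted up for the dead. The article does not support either. A person who has died has left the target population and has no outcome at M_t. The list in section 2.4 defines the gross response rate used for sizing, not the target of the XGBoost model. Table 2 places death under frame incidences with direct removal, and Table 4 lists no death variable; only the civil-registry origin of the BDLPA (section 2.3) suggests that deaths could be identified. What remains is that no section says whether deaths are taken out before the model is fitted.
- **Direction.** A reader might infer that the contrast in hypothesis 1 is necessarily pulled towards no difference. Long admission, disability and illness also remove undiagnosed people, so the direction is not established. Moreover, the change tables in section 2.10 are segmented by demographic and territorial variables. A contrast by diagnosis would come from the mixed models, and the article does not say how weights enter those.
- **Size.** The response rates by admission status are invented. Only long-term admissions are named as a cause of loss, interviews can be postponed, and a relative may answer for someone unable to. Sampling error is also large: 7.1% of 3000 is about 212 diagnosed people, with a 95% half-width of 1.96 × √(0.25 × 1.8 / 212) = 9.0 points, against an illustrated loss of 0.6 to 2.9 points.
- **Feasibility.** Section 1.2 describes epidemiological data over one year and clinical data over two, so cover of the months before M5 is not established. ESSOC+55 is drawn from Guadalinfo users, and its linkage is not described.
- **Openness to alternatives.** Section 2.8 mentions auxiliary information and promises to investigate other variables. It names none from the registries, so the specified model is unchanged.

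None of this removes the core: the weights as specified cannot see an interim infection or admission.

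**Conclusion.** The point holds for infection and hospital admission. The specified model stops at M_t-1. The article itself ties illness and long admission to loss and COVID-19 to outcome, and it already plans to extract the registry data that would fill the gap.

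Neither size nor direction can be derived from the article. The figures of 0.1 to 1.5 points for a panel prevalence and 8–29% for a contrast are illustrations on assumed inputs and should not be quoted as estimates of bias. This is a cheap and worthwhile improvement to the weighting, not an error that invalidates the study.

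**What to change.** In section 2.8 and Table 3:

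1. Add to the XGBoost predictors the SVEA positive test, hospital admission and ICU stay, and BPS health-care use or change in chronic disease, dated between M_t-1 and M_t. Take them from the registries, not from the M_t interview.
2. Run the linkage on the whole M_t-1 effective sample, and extend the SVEA and BPS extraction to cover the gap before M5.
3. Where deaths can be identified, remove them as ineligible before the model is fitted. Do not use death as a predictor.
4. Recompute the ESSOCgeneral longitudinal weights for the measurements already taken and use the same model at M5. Apply it to the second ESSOCzones measurement and, where linkage is possible, to ESSOC+55.

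The cost is plan wording, a linkage step for dropouts and somewhat more variable weights. No new fieldwork is needed and no sample size changes.
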